**Table 5 Tab5:**
[figure not shown]
Power under various conditions. Green indicates power greater than or equal to 90%

### Qualitative data collection and analyses

At the end of the 2-year intensive implementation phase, we will conduct focus group discussions (FGDs) among each facility-level improvement team (*n* = 16) to collect in-depth qualitative data on CFIR constructs of interest (Table 6). Questions will be sourced from CFIR interview guides (http://cfirguide.org/), supplemented by targeted elicitation of satisfaction with tools/protocols, intent-to-continue-use, and deviations from SAIA protocols. FGDs will occur after primary quantitative analyses, with facilities classified as high, medium, or low performing in terms of fidelity to SAIA-MH as well as cascade improvements. By classifying clinics, we intend to uncover salient features and determinants of successful implementation. Following analyses of mechanisms of effect, we will also classify a sub-set of individual staff (*n* = 10–20) and facilities (*n* = 4–6) into groups who showed large improvements in causal mechanistic pathways and those with little improvement across targeted mechanisms. These staff will be targeted for additional in-depth-interviews (IDIs, individuals) or FGDs (facilities) organized around the CFIR and paired with targeted elicitation of qualitative explanatory data on barriers/facilitators to specific mechanisms of action. These data will help: (1) inform the need for tailoring of SAIA-MH for specific facility and individual-level contexts that may hinder or enhance mechanism activation; (2) understand other potential moderators, mediators, preconditions, or mechanisms not captured in current causal pathway models; and (3) further unpack the mechanistic reasons SAIA-MH may show effects in some settings, and for some individuals, and not others. To refine models and understand implementation mechanisms, processes, and determinants under routine conditions, both rounds of FGDs and IDIs will be repeated at the end of the sustainment phase. IDIs and FGDs will be conducted in Portuguese by an experienced facilitator accompanied by a note-taker, audio-recorded, and transcribed verbatim into Portuguese by trained Mozambican staff. Using existing CFIR codebooks as a guide, two researchers will use a stepwise, iterative process to review transcripts and identify key deductive themes (using select CFIR constructs, implementation outcome, and targeted mechanism themes) while allowing for flexibility of other inductive themes to emerge. Following iterative coding of transcripts, the team will convene with the PI to identify coding discrepancies with the coding process repeated until consensus is achieved.

**Table 6 Tab6:**
[figure not shown]
Consolidated Framework for Implementation Research (CFIR) constructs of interest

### SAIA-MH mechanisms assessment approach

Using theoretical bases informing SAIA implementation strategy development, a review of literature for similar distinct implementation strategies (audit and feedback [65–69], quality improvement [70–75], facilitation [76, 77]), and mixed-methods quantitative [27] and CFIR qualitative data [27] from the original HIV-focused SAIA trial and the SAIA-MH pilot study, we have developed an initial causal pathway model to test in the present study (Fig. 4). Each moderator, precondition, and hypothesized mechanism will be measured each month during baseline, intensive implementation, and sustainment periods across all 8 intervention and 8 attentional placebo control facilities during facility-level facilitation/supervision visits. For clarity, we hypothesize that attentional placebo controls will show no significant activation of SAIA-MH mechanisms but will account for key threats to validity such as testing, maturation, external shocks, and Hawthorne effects. Mechanisms will be assessed monthly at the individual provider level and then aggregated within facilities across time, while MH cascade performance will be sourced from individual patient CommCare records and then aggregated within facilities across time. Primary analyses of mechanisms will occur after the intensive phase (Table 2). Secondary analyses will occur at the end of the sustainment phase.

### SAIA-MH mechanisms assessment power

Overall, this study was powered to specific aim 1a examining mean treatment effects of SAIA-MH on MH treatment cascade performance. Given the paucity of literature on methods, theories, and frameworks underlying mechanisms of multicomponent implementation strategy effects, this aim will focus on an exhaustive examination in search of practically and clinically meaningful mechanism, moderator, and precondition effect estimates for further examination in subsequent research. The goal of this aim is to contribute to theory building to inform future studies specifically powered to test hypothesized causal pathway models. No confirmatory hypothesis testing driven by *p* value inference will be performed, as recommended when conducting exploratory studies by Leon (2011) [78]. That said, we will have a sufficient sample size to have stable effect estimates with reasonable precision based on our design including 6 baseline measurements and 24 implementation measurements among a minimum of 3 providers across all 16 facilities. Assuming an intra-cluster correlation coefficient of 0.25 [20], if a binary mechanism leads to a function improvement odds ratio of 1.5, we will have > 0.85 power to detect the indirect effect with variance of the mediator assumed to be 0.5. Continuous mechanisms will have appreciably higher power.

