### Primary study power assessment

In the pilot, SAIA-MH increased patient functional improvement with an adjusted odds ratio of 3.7 and an absolute increase of 8.9% (4.2% control; 13.1% intervention) [25]. The intra-cluster correlation coefficient using outpatient mental health data in the same setting is estimated at 0.26 [https://pophealthmetrics.biomedcentral.com/articles/10.1186/s12963-015-0043-3]. Selected clinics in Table 4 conducted an average of 774 outpatient MH visits per 6 months in 2019–2020. In the pilot, 40% of patients returned for follow-up within 60 days in control periods; thus, we estimate target clinics will see approximately 300 follow-up patients per 6 months. Using these assumptions, we will have ≥ 90% power to detect an increase as small as 2.2% in functional improvement (primary), 3.6% for adherence (secondary), and 4.9% for retention (secondary); (Table 5).

**Table 4 Tab4:** Facility-level characteristics

Facility	Province	Mean annual outpatient mental health visits 2019–2020	Level	Number of psychiatric technicians	Number of psychologists	Minutes to drive from Provincial Capital
Nhamatanda	Sofala	4000	Rural hospital	2	3	90
Dondo Sede	Sofala	2885	Urban health center type A	1	3	40
Macurungo	Sofala	1588	Urban health center type A	1	1	15
Mafambisse	Sofala	1306	Rural health center type 1	1	1	30
Chingussura	Sofala	981	Urban health center type A	1	2	26
Mascarenhas	Sofala	752	Urban health center type B	1	2	16
Muxúngue	Sofala	1107	Rural hospital	1	1	180
Inhamizua	Sofala	664	Urban health center type B	1	1	30
Manica	Manica	3605	District hospital	2	2	1
Gondola	Manica	1314	District hospital	2	1	20
Catandica	Manica	983	District hospital	2	2	120
Sussundenga Sede	Manica	964	Rural health center type 1	1	2	60
Macate	Manica	466	Rural health center type 2	1	1	60
Nhamaonha	Manica	284	Urban health center type B	1	1	10
Vila Nova	Manica	195	Urban health center type A	1	1	15
Vanduzi	Manica	3675	Rural health center type 1	1	1	30

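### The power quoted for the mechanism analysis gives a binary mediator a variance of 0.5, twice the largest value that a 0/1 variable can have

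*Protocol article*

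**What the plan says.** The section on mechanisms assessment power says that the trial is powered on Aim 1a and that the mechanism work is exploratory: "No confirmatory hypothesis testing driven by" p-values is planned. It then rests the stability of the estimates on "6 baseline measurements and 24 implementation measurements among a minimum of 3 providers across all 16 facilities" and adds a power figure. The inputs to that figure are "Assuming an intra-cluster correlation coefficient of 0.25", an effect size ("if a binary mechanism leads to a function improvement odds ratio of 1.5"), and a mediator variance. The result is more than "0.85 power to detect the indirect effect with variance of the mediator assumed to be 0.5". The closing sentence adds that continuous mechanisms would do better still.

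Two neighbouring sections matter. The section on the mechanisms assessment approach says: "Mechanisms will be assessed monthly at the individual provider level and then aggregated within facilities across time". The section on mechanisms assessment analyses defines the indirect effect as the product of two path coefficients: strategy to mechanism, and mechanism to outcome.

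**The concern.** One sentence calls the mediator binary and gives it a variance that no 0/1 variable can have. In the usual power formula for a mediator, information on the mechanism-outcome path is proportional to the mediator variance, so a value twice the attainable maximum would matter if it really entered the calculation. The figure is the only numerical power statement for Aim 1b, and the remark about continuous mechanisms is made relative to it.

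A second, smaller question is what the figure describes. It is labelled as power for the indirect effect, but the only effect size shown with it is the mechanism-outcome odds ratio of 1.5.

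**Working it through.** **Bound on the variance.** For a 0/1 variable with prevalence q, the variance is q(1−q). It peaks at q = 0.5, where it is 0.25 and the standard deviation is 0.5. The stated 0.5 is therefore twice the maximum variance, and exactly the maximum standard deviation. Averaging providers within a facility does not help: a mean of 0/1 values stays between 0 and 1, so its variance also cannot exceed 0.25.

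**Can the stated figure be reproduced?** Not uniquely. The section does not give alpha, the outcome proportion, the correlation between arm and mediator (ρ), or how clustering entered. I used the standard formula for a logistic outcome:

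power = Φ( |ln OR| × SD × √[ n_eff × p(1−p) × (1−ρ²) ] − 1.96 )

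Inputs from the article:
- ln 1.5 = 0.405
- (6 + 24) × 3 × 16 = 1440 provider-months
- ICC 0.25
- outcome proportions from the section on primary study power: "absolute increase of 8.9% (4.2% control; 13.1% intervention")

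My assumptions are two-sided alpha of 0.05 and, for illustration, clustering over the 3 providers only. That gives a design effect of 1 + 2 × 0.25 = 1.5 and n_eff = 1440/1.5 = 960. The value p = 0.5 is also an assumption.

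| Reading of 0.5 | p | ρ | Argument before subtracting 1.96 | Power |
|---|---|---|---|---|
| Variance (SD 0.707) | 0.131 | 0 | 2.997 | 0.850 |
| Same, with variance cut to 0.25 | 0.131 | 0 | 2.119 | 0.563 |
| SD (variance 0.25) | 0.5 | 0 | 3.141 | 0.881 |
| SD (variance 0.25) | 0.5 | 0.3 | 2.996 | 0.850 |

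Both readings can be made to give 0.85, so the figure does not reveal which was used.

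**If 0.5 was entered as a variance.** Power 0.85 corresponds to 1.960 + 1.036 = 2.996. Moving to the best attainable variance multiplies this by √(0.25/0.5) = 0.707. The other unstated inputs cancel.

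| Power at variance 0.5 | Argument | × 0.707 | Power at variance 0.25 |
|---|---|---|---|
| 0.85 | 2.996 | 2.119 | Φ(0.159) = 0.56 |
| 0.90 | 3.242 | 2.292 | Φ(0.332) = 0.63 |
| 0.95 | 3.605 | 2.549 | Φ(0.589) = 0.72 |

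The last two rows are there because the article says more than 0.85. All results assume 50% prevalence; any other prevalence gives less.

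**If 0.5 was meant as the standard deviation.** The variance is 0.25 and the figure is the best case at 50% prevalence. Taking power as exactly 0.85 there, and using assumed prevalences because the article gives none:

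| Prevalence | Variance | 2.996 × √(variance/0.25) | Power |
|---|---|---|---|
| 40% | 0.24 | 2.936 | 0.835 |
| 30% | 0.21 | 2.746 | 0.78 |
| 20% | 0.16 | 2.397 | 0.67 |

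**The case against.** The strongest reply is that 0.5 is simply a mislabelled standard deviation. That is plausible, because 0.5 is exactly the largest standard deviation of a 0/1 variable, and the check above shows that the power could then stand. A reader might infer that the information is overstated at least two-fold and the true power is 0.56. The article does not support that as a flat statement: it follows only if 0.5 entered as a variance.

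Another coding could also rescue the number. With −1/+1 coding the variance is 4q(1−q), which can equal 0.5. No such coding is described, and an odds ratio of 1.5 per unit would then be 1.5² = 2.25 between the two categories, which is not the natural reading of the sentence.

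Three further inferences should be resisted:
- That absent mechanisms will be reported as tested with 85% power. The section says the aim is exploratory, that the trial is powered elsewhere, and that the results are to inform later studies powered for the purpose. It also rests stability on the number of repeated measurements; the power figure follows as an illustration.
- That quoting power contradicts the absence of p-value testing. Only confirmatory testing is ruled out, and the figure is introduced as a qualification. Preferring an expected interval width would be a matter of taste.
- That the missing size of the strategy-to-mechanism path is an error. A condensed article may leave it to the full protocol. What remains is conditional: if only the odds ratio of 1.5 entered the calculation, the label does not match the article's own definition of an indirect effect.

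None of these replies makes a variance of 0.5 possible for the 0/1 mediator described.

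**Conclusion.** The concern holds as an impossible or mislabelled input. That part needs no assumption beyond 0/1 coding, the only coding that the sentence suggests. The effect on the power is undetermined. If 0.5 was used as a variance, 0.85 falls to at most about 0.56, with all other inputs unchanged and two-sided alpha of 0.05. If it was a standard deviation, only the wording and the unstated prevalence need attention, and the figure is an upper limit over prevalence. The documents do not show that the power is in fact overstated. The matter is confined to an exploratory aim: the Aim 1a comparison and the number of clinics do not depend on it.

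**What to change.** 1. Check in the original calculation whether 0.5 was used as a variance or as a standard deviation, and correct the label.
2. Recompute with variance q(1−q) at a stated mechanism prevalence, preferably over a short range, and restate the power for this exploratory aim. Giving the alpha, outcome proportion and effective sample size alongside would make the figure checkable.
3. If only the mechanism-outcome odds ratio entered the calculation, call the result power for that path. If both paths entered, say so.
4. Check that the remark about continuous mechanisms still holds against the corrected figure.

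The cost is a recalculation and one rewritten sentence, possibly with a less favourable number. Design, sample size and the primary analysis stay as they are.

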### SAIA-MH mechanisms assessment analyses

Our analytical plan will progress in 3 stages and across 3 separate patient-level outcomes: functional improvement (primary), medication adherence (secondary), and retention (secondary). Repeating the analytic process across 3 dependent variables provides built-in replication, allowing the identification of consistent effects (direct, indirect, and moderated). First, we will conduct univariate examination of hypothesized mechanism effects using multi-level longitudinal SEM accounting for multiple providers nested within facilities across time. The purpose of this will be to examine single main effect estimates for hypothesized mechanisms. For example, we will estimate a univariate multi-level longitudinal SEM of SAIA-MH strategy effect predicting changes in teamwork, then predicting MH treatment cascade outcomes (Fig. 4). We will conduct diagnostics, including assessing linearity of mechanism effects, model residual distributions, and variance accounted for in mechanisms and outcomes. We will then test potential moderators in univariate models, in search of those that strongly affect strength or direction of univariate effects. Moderators will be examined for their effect on SAIA-MH strategy activation of mechanisms (left side of Fig. 4) as well as mechanism effects on outcomes (right side of Fig. 4); preconditions will be tested alongside moderators. Second, we will include all mechanisms simultaneously in a multivariable longitudinal multi-level SEM. Including all mechanisms, even those showing no effects in univariate models accounts for potential suppressor effects [79]. Moderators that showed meaningful effects in univariate models will then be included in a final multivariable model. Final model diagnostics will be verified, and variance accounted for in mechanisms, as well as outcomes, will be reported. This multivariable model will allow examination of (1) mechanisms most affected by SAIA-MH (left side Fig. 4); (2) mechanisms that had an effect on outcomes (right side Fig. 4); and (3) the product of #1 and #2 path coefficients indicating the indirect effect of SAIA-MH on treatment outcomes operating through a given mechanism. Separating out paths #1 and #2 can inform improvement of the SAIA-MH strategy; for example, if a mechanism had a large effect on outcomes (path #2), although was only weakly activated by SAIA-MH (path #1), the SAIA-MH strategy could be modified to enhance activation of this potentially high-leverage mechanism. Findings from path analyses will be incorporated into targeted elicitation of explanatory qualitative information during the second round of CFIR interviews. Individuals/facilities will be classified into those showing large mechanism changes compared to those with little improvement.

### Costs

We will conduct activity-based costing and time and motion observation at both intervention and control clinics to estimate the incremental cost of implementing SAIA-MH. Throughout study implementation, we will estimate all costs that would be incurred by the Ministry of Health to administer the SAIA-MH intervention. These costs will be collected and tabulated using activity-based cost menus during start-up, intensive implementation, and sustainability periods. Costs include patient visits, medication, personnel, supervision, supplies, buildings and overhead, strategy delivery, facility support for systems changes, training, and equipment. Time-motion observations following protocols previously used by our group in Mozambique [80] will estimate personnel time needed for SAIA-MH tasks.

### Economic evaluation

We will develop a Markov cohort model using R software reflecting the natural history of MH disease progression and disability, and treatment, which has been used for previous cost-effectiveness analyses of MH interventions in LMICs [81–87]. The model will simulate a cohort with different MH conditions stratified by retention in care, medication adherence, and functional improvement. We will parameterize the model with cost and outcome data from the SAIA-MH cluster RCT and facility-level contextual data (patient loads and trends; human resources; facility types) and demographic data (gender; age distributions). In line with previous studies and economic guidelines [81, 88], costs and effectiveness will be discounted at 3% annually (varied from 0-5% in sensitivity analyses). Disability weights for DALYs will be obtained from the Global Burden of Disease 2017 [89]. Scale-up scenarios will model changes in patient retention, adherence, and functional improvement based on study results and varied in sensitivity analyses. Prior to conducting cost-effectiveness analyses, we will assess model validity/reliability by evaluating our model’s ability to accurately project trends in care cascade outcomes (retention, medication adherence, functional improvement).

We will simulate the health and economic impacts of scaling-up the SAIA-MH implementation strategy in Mozambique at district, provincial, and national levels. Health outcomes include effects on the outpatient mental health cascade (proportion retained, medication adherent, and with functional improvement). The model will estimate the effects of scale-up scenarios on: (1) retention and adherence in MH care by diagnosis; (2) functional improvement by diagnosis; and (3) Disability Adjusted Life Years (DALYs) [88] averted, cost per DALY averted, and budgetary impact from the payer (Ministry of Health) perspective. Different scenarios will examine rate and breadth of expansion (number/characteristics of future facilities/districts/provinces). We will estimate incremental costs, as well as treatment costs incurred and averted due to the implementation strategy.

We will project SAIA-MH effects on functional improvement, adherence, and retention compared to standard of care. We will calculate the cost per mental health patient achieving functional improvement and the incremental cost-effectiveness ratio (ICER) per new mental health diagnosis and DALY averted for each scale-up scenario. Analyses will be from the payer perspective, using economic productivity data to estimate mental health disability averted and incorporating costs of healthcare to evaluate economic impact.

## Discussion

This study is innovative in extending a breakthrough from the field of HIV to MH treatment, while also being the first to assess not only *whether* the SAIA implementation strategy works—but *how* it works—through testing causal pathway models. Systematic reviews of implementation strategies for mental health have found that nearly half produce no statistically significant effects on targeted implementation or clinical outcomes [90]. Leaders in the field have advocated that future studies testing implementation strategies specify strategy-mechanism-outcome linkages and test these mechanisms through causal pathway analyses [91]. Causal pathway analyses, and the specification of mechanisms of effect, are necessary to: (1) better understand why unsuccessful strategies fail; (2) inform the development of more effective and efficient implementation strategies; (3) identify mutable targets for future strategies; and (4) inform tailoring and matching strategies to barriers and contexts [91, 92]. Despite this urgent need in the field, a systematic review found that of 88 RCTs testing implementation strategies for mental health, zero met minimum criteria necessary for testing mediation hypotheses [92]. Mechanistic models of effect are needed to match/tailor strategies to barriers/contexts, prioritize strategy use, and expedite the development of more effective, efficient, and feasible strategies.

Applying the SAIA implementation strategy to task-shared MH systems optimization will distinguish between the “hard core” and “adaptable periphery” of the SAIA strategy, as well as its “transferability” to other disease areas and treatment cascades. Understanding which components of an implementation strategy are essential to effectiveness and which components may be adapted to suit context is critical to informing strategy scale-up. The present study provides a unique opportunity to distinguish between these components. By fixing the contextual determinants and modifying the application of SAIA, this study builds directly from prior studies and will directly inform which components are essential to effectiveness across disease areas [27, 29]. This project will also help generate an understanding of the overall “transferability” of the SAIA strategy to meet the needs of different treatment cascades or disease areas [93, 94]. Data on SAIA-MH effectiveness, determinants of implementation success, and mechanisms of effect (or non-effect) will be used to inform the use of SAIA across varied local contexts and complex treatment cascades. We believe that our focus on testing the multicomponent SAIA-MH strategy to optimize the linked MH cascade rather than a single intervention on a single siloed health indicator is innovative. Furthermore, the SAIA strategy has longevity because, rather than testing a single intervention that may become irrelevant after policy, system, or technology changes, SAIA-MH packages protocols and tools for data-driven systems optimization appropriate for the changing landscape of health delivery systems across LMICs.

Extending breakthroughs of implementation strategies for HIV treatment cascade optimization to MH care is an efficient and promising method for scientific advancement. The original “Systems Analysis and Improvement Approach” (SAIA) implementation strategy improved HIV treatment cascade performance and was accessible/user-friendly for frontline workers/managers [27, 29, 95]. In our preliminary developmental/exploratory project, SAIA-MH showed strong promise for mental health treatment cascade gains [25]. While pharmacological treatment for MH has system idiosyncrasies compared to HIV, both MH and HIV are chronic illnesses requiring screening/identification in multiple settings, referral to a centralized treatment center with information systems enabling longitudinal care, intra- and inter-facility referrals for pharmacy, laboratory, or other support services, and facility-community linkages to manage case-finding, medication management, and patient follow-up. For these reasons, proven strategies developed for the HIV cascade are ideal scientific building blocks for the development of strategies for MH treatment cascade optimization. If effective, the SAIA-MH implementation strategy has a large potential to be rapidly scaled-up to decrease gaps in task-shared MH treatments globally.

